While interventions should be developed for patients with all severities of COPD, it is logical to target immediate efforts towards patients with ‘high-risk’ COPD, that is, those who are at most risk of exacerbation and hospital admissions. Established data indicate that patients with COPD who have had severe exacerbation (one requiring ED attendance or hospital admission) in the previous 12 months and/or have persisting hypercapnic respiratory failure requiring home NIV fall into this high-risk group.^6 13^ Interventions proven in this group can then be rolled out (if cost-effective) to the lower risk groups of patients with COPD.

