### Study population

People with high-risk COPD attending secondary care in the North and South Sectors of NHS GG&C will be screened for inclusion in this study.

Inclusion criteria:

Confirmed diagnosis of COPD, established prescreening or at screening, defined as per Global Initiative for Chronic Obstructive Lung Disease (GOLD) 2020 guidelines.^6^Home NIV cohort: hypercapnic respiratory failure and/or sleep disordered breathing, meeting established criteria for provision of home NIV.Exacerbation cohort: presentation within last 12 months with severe or life-threatening exacerbation of COPD, defined as per GOLD 2020 guidelines.^6^Participant or close contact who has daily access to smartphone, tablet or home computer with internet access.Informed consent.>18 years of age.

Exclusion criteria:

Inability to comprehend informed consent.Communication barrier precluding use of COPD digital service.

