### Sample size

Previous NHS GG&C studies,^10 21^ combined with internal audit data (showing that 80% of patients have direct or daily smartphone, tablet or web access), indicate that recruitment of 400 participants across a 12-month period is feasible, and likely to provide adequate data to conduct meaningful primary and secondary endpoint analyses.

An improvement in admission-free survival, with reduction in admissions by one per patient per year is projected, if support for provision of evidence-based COPD care is achieved by the service model. As the feasibility of an end-to-end digitalised service model for COPD has not yet been tested, and the service components will be adapted during the study, sample size power calculations and randomisation are not yet appropriate.

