### Screening and eligibility assessment

Participants will be identified from ED attendance, hospital admission or COPD multidisciplinary team referral. It is anticipated that the majority of participants will be identified and recruited during their index acute admission.

Review of focused medical history and lung function test results will be undertaken as part of screening evaluation to ensure all inclusion and no exclusion criteria are met.

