## Study outcome measures

Primary and secondary endpoints for the RECEIVER Study are shown in table 1.

**Table 1 T1:** RECEIVER primary and secondary endpoints

Primary endpoint	Proportion of enrolled high-risk participants with COPD who use remote management in a digital service model
Secondary endpoints	Clinical outcomes, comparing impact of digitally enabled remote management versus historical and contemporary SafeHaven cohorts: Clinical events: COPD exacerbation; unscheduled care contact (digital platform, COPD team visit, primary care, emergency department, hospital admission); mortality—COPD and non-COPD related. Hospital occupied bed days preceding and subsequent 12 months (adjusted time interval if survival <12 months). Treatment uptake (where indicated): smoking cessation; pulmonary rehabilitation; vaccination; supported self-management; home oxygen; home NIV. NIV group: NIV usage, symptom change, NIV therapy parameters, blood gases during routine clinical care. Supported self-management: utilisation of self-management information (page views), number of exacerbation managed at home versus in hospital, number of rescue packs used in 12 months (captured through weekly PROs), utilisation of messaging (number of message threads), sputum microbiology (where available during routine clinical care), impact of patient activation measures (where measured during routine care). Impact of demographics, physiology and patient activation measures (where measured during routine care)—deprivation category of area of residence, age and sex, number of previous admissions, smoking status, participation in pulmonary rehabilitation in previous 2 years; lung function measurements, modelled home air pollution exposure; EMG, oscillometry and home air pollution monitoring in subset of participants where this is carried out—on outcomes, clinical events and treatment uptake. Clinical service outcomes for digital service model, remote-managed home NIV and supported self-management: Remote-managed home NIV: number, nature and complexity of NIV therapy reviews and interventions to provide. Supported self-management: number, nature and complexity of reviews and interventions to provide. Digitalised service model: user and developer time/cost required for development and modification of clinical dashboard; qualitative analysis (clinical user satisfaction and reflection on efficiency or additional workload); quantitative analysis (clinical dashboard utilisation tracking). Patient portal: user and developer time/cost required for development and modification of clinical dashboard; qualitative analysis (user satisfaction) and quantitative analysis (uptake, engagement with app and wearable, successful use of digital service vs bypass to conventional healthcare contacts). Machine learning-supported exploratory analyses of associations and relative predictive importance of electronic health record, PROs, wearable physiology and NIV parameters: Associations between changes in PROs (MRC, CAT, symptom diary, and EQ-5D-5L questionnaires) with routine clinical care interventions, COPD exacerbation and other clinical events. Associations between changes in wearable monitoring parameters (activity, sleep, heart rate variability, energy expenditure, respiratory rate) with routine clinical care interventions, COPD exacerbation and other clinical events. Associations between changes in NIV-monitored parameters (usage, leak, airway pressures, respiratory rate, tidal volume, minute ventilation, inspiratory/expiratory ratio and detected respiratory events) with routine clinical care treatment interventions, COPD exacerbation and other clinical events. Associations between changes in clinical endpoints and relative importance plots of all remote management-acquired data (including EMG, oscillometry and home pollution monitoring exploratory endpoints in subgroup these measured on) to determine contribution of these to outcome prediction, and therefore value of these for future prospective study. Patient-centred outcomes: Health-related quality of life (EQ-5D-5L) at baseline and monthly during study. Qualitative user research (planned subset of participants, convenience sample) with semistructured user experience interviews. Impact of patient activation (where this is measured at baseline and/or follow-up during routine clinical care) on enrolment and use of digital service model. Healthcare cost analyses: Development and installation costs for digitalised service model for remote management of COPD. Recurring costs (clinical staffing, digital platform hosting, digital platform scheduled update and maintenance) for digital service model for remote management of COPD. Projected direct and indirect cost-savings (admission and unscheduled care reduction, travel, carer burden impact, clinical efficiency) of high-risk COPD with digitally enabled remote management, compared with previous service model.

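### The before and after bed-day windows have no rule for the qualifying admission, so a fall within the RECEIVER cohort is expected with no service effect, and the controls remove it only if anchored equivalently

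*Protocol article*

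**What the plan says.** The relevant statements are spread over several sections of the protocol article.

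- **Study outcome measures, Table 1.** The endpoint is "Hospital occupied bed days preceding and subsequent 12 months", with the interval adjusted for people who survive less than a year. The group it belongs to is headed as "comparing impact of digitally enabled remote management versus historical and contemporary SafeHaven cohorts".
- **Subsequent assessments.** Secondary endpoints are observed for 12 months from recruitment, which makes recruitment the natural dividing date. Table 1 itself names no anchor.
- **Study population.** The exacerbation cohort qualifies by "presentation within last 12 months with severe or life-threatening exacerbation of COPD". The home NIV cohort qualifies by "hypercapnic respiratory failure and/or sleep disordered breathing, meeting established criteria for provision of home NIV", which requires no admission.
- **Introduction.** A severe event is described as "severe exacerbation (one requiring ED attendance or hospital admission) in the previous 12 months", so an ED attendance alone is enough.
- **Screening and eligibility assessment.** "It is anticipated that the majority of participants will be identified and recruited during their index acute admission".
- **Sample size.** An improvement in admission-free survival, "with reduction in admissions by one per patient per year is projected". No reference level is given.
- **Study design; Statistics and data analysis.** Controls are matched on demographics, severity and admission frequency. They are selected on a severe exacerbation between 1 January 2010 and 30 April 2019 (historical) or between 1 July 2019 and 30 June 2020 (contemporary). No index date is given for a control, and nothing says whether the qualifying event counts in the matching.

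**The concern.** When people enter a cohort because of an event, the year that ends at entry contains that event by design and the next year does not. A before-after comparison then shows a fall even if nothing changes. Here the fall is of the same order as the only effect size that the article projects.

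Most recruits are in hospital at consent, so their index stay also crosses the dividing date, and no rule says which window receives it. The sign and size of the before-after change therefore depend on a choice that is not stated. Table 1 also plans projected cost-savings from fewer admissions, measured against the former service model. That comparator is not expressly the matched cohorts, so a within-cohort fall could enter the savings.

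**Working it through.** **The plan's own figure.** The projected one-admission reduction cannot be reproduced, because the article gives no admission rate, reference level or derivation. The planned 400 participants rest on feasibility, and power calculations are explicitly declined.

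**Inputs.** From the article: 12-month windows, a qualifying event in the last 12 months, and a majority recruited at the index admission. Assumed, because the article gives no values: admission rate λ of 0.5 to 3 per patient-year, index stay of 4 to 8 days, recruitment mixes as below. Throughout there is no service effect and each patient's rate is constant.

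**A. Recruited at the index admission, counted as before.** Before = 1 + Poisson(λ) and after = Poisson(λ). The expected fall is (1 + λ) − λ = 1.00 at any λ. With gamma-distributed patient rates, simulation gives 0.997 to 1.003. If all 400 enter this way with λ = 2, a paired test favours the service in 100% of simulations. If the index admission is counted as after, the same arithmetic gives a rise of 1.00.

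**B. Recruited at a random time, given at least one admission in the past year.** Fall = λ/(1 − e^−λ) − λ = λe^−λ/(1 − e^−λ).

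| λ per year | 0.5 | 1 | 1.5 | 2 | 3 |
|---|---|---|---|---|---|
| Fall | 0.77 | 0.58 | 0.43 | 0.31 | 0.16 |

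With gamma-distributed rates of mean 1 to 3, the fall is 0.23 to 0.53.

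**C. Mixed cohort.** Fall = (share by A) × 1 + (share by B) × (fall from B) + (share with no qualifying admission) × 0.

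| Shares A / B / none | λ = 1 | λ = 2 | λ = 3 |
|---|---|---|---|
| 50% / 25% / 25% | 0.65 | 0.58 | 0.54 |
| 60% / 20% / 20% | 0.72 | 0.66 | 0.63 |
| 60% / 30% / 10% | 0.77 | 0.69 | 0.65 |
| 80% / 10% / 10% | 0.86 | 0.83 | 0.82 |

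The range is 0.54 (0.50 + 0.25 × 0.157) to 0.86 (0.80 + 0.10 × 0.582).

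**Bed days.** If the whole index stay counts as before, route A contributes share × stay, from 0.5 × 4 = 2 to 1.0 × 8 = 8 days per patient. If a fraction q of a stay of L days precedes consent, the net fall for that patient is qL − (1 − q)L = L(2q − 1). This is zero at q = 0.5 and negative below it. For example, L = 6 and q = 1/3 give 6 × (−1/3) = −2, a rise of 2 days.

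**D. Against controls.**

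- Both cohorts anchored at an equivalent qualifying admission: each changes by −1.00, and the simulated difference is −0.001. The artefact cancels.
- Controls anchored at their first event in the selection window: their fall is 0.21 to 0.74. This was simulated with gamma shape 0.7 to 3, mean rate 0.5 to 2 per year, and windows of 1 and 9.33 years. Against index-recruited participants it leaves a spurious benefit of 1.00 − 0.74 = 0.26 to 1.00 − 0.21 = 0.79.
- Controls anchored at their last event: their fall is about 1.3 to 1.8, which leaves a spurious harm of about 0.3 to 0.8.
- Controls all anchored at a random qualifying admission (fall 1.00) against the mixed cohort in C: the difference runs against the service by 1.00 − 0.86 = 0.14 to 1.00 − 0.54 = 0.46.

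**The case against.** The strongest reply is that the article's stated comparator is the SafeHaven cohorts. They are matched on admission frequency and are themselves selected on a severe exacerbation. With equivalent anchoring the artefact disappears, as D shows. That stands, and the defect is therefore conditional. But the article does not require equivalent anchoring. Controls have no recruitment date, the historical selection window spans more than nine years in which a patient may have several events, and home NIV entrants need no event while every control does.

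A second reply is that index dates are operational detail for a full protocol or analysis plan, neither of which is at hand. In part this is fair. But Table 1 already fixes a before and after window, and the entry criteria make the two halves unequal, so the point goes beyond missing detail.

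Third, bed days are one of many secondary endpoints in a feasibility study whose primary endpoint is use of the service, and Study limitations accepts an inherent risk of bias. This limits the severity. That section does not identify this bias or control it.

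Three stronger readings are tempting and are not supported:

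- A reader might infer that the projected reduction is itself defined as before versus after, so that the artefact would reproduce it exactly. The Sample size section gives no reference level, and no rule declares the projection met.
- A reader might take the loss to be a full admission, or a full index stay, for each of the 400. ED-only, home NIV and later-recruited entrants, and stays split at consent, all lower it.
- A reader might state as fact that controls are indexed on a coded event and participants on recruitment. The article gives no index date for controls, and none for this endpoint in either group.

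**Conclusion.** The point holds in conditional form. As the windows are written, a before-after fall in the RECEIVER cohort is expected without any service effect and cannot be read as one. If the index admission counts as before, the fall is about 0.5 to 0.9 admissions per patient under the assumed rates and mixes, with 1.00 as the upper limit. That is the same order as the projected reduction. If the index stay counts as after, the bias shrinks or reverses.

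The between-cohort comparison is sound only if controls are anchored equivalently. An unstated choice of control event could shift the difference in change by roughly 0.3 to 0.8 admissions in either direction. All these sizes rest on assumed admission rates, stays and recruitment shares, and on constant risk within a patient. The severity is moderate.

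**What to change.** - **Table 1, index event.** Leave the qualifying admission or attendance out of both windows, or assign it to the same window, in all three cohorts. Give controls an equivalent index date, with the same lag from event to start of follow-up where recruitment came later. Identical treatment matters more than the deduction: under route B with λ = 1, simply removing one event leaves 1.58 − 1 = 0.58 before against 1 after, which over-corrects.
- **Home NIV entrants without a qualifying event.** Use the recruitment date with controls anchored to match, or report this group separately.
- **Effect estimate.** Make it the between-cohort comparison of the later window, adjusted for the earlier one. Label the within-RECEIVER change descriptive, and do not use it for the projected cost-savings.
- **Sample size section.** State the projected reduction relative to the matched controls' follow-up rate.

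The cost is wording in Table 1, Sample size, and Statistics and data analysis, plus a little more analysis work. No new data are needed. The downside for the sponsor is that the apparent before-after benefit becomes smaller.

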**Methods and analysis:**

The Remote-Management of COPD: Evaluating the Implementation of Digital Innovation to Enable Routine Care trial is a prospective observational cohort hybrid implementation and effectiveness study that will explore the adoption of a digital service model for people with ‘high-risk’ COPD and evaluate the feasibility of this approach versus current standards of care. People with COPD, who have had recent severe exacerbation and/or COPD–obstructive sleep apnoea overlap or chronic hypercapnic respiratory failure requiring home non-invasive ventilation (NIV) or continuous positive airway pressure (CPAP), with internet access will be recruited into the study and enrolled into the digital service.

Study endpoints will examine participant utilisation, clinical service impact and clinical outcomes compared with historical and contemporary control patient data. The digital infrastructure will also provide a foundation to explore the feasibility of approaches to predict outcomes and exacerbation in people with COPD through machine learning analysis.

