**Figure 1 F1:**
[figure not shown]
RECEIVER Digital Service ComponentsCOPD, chronic obstructive pulmonary disease; EHR, electronic health record; NHS GG&C, National Health Service Greater Glasgow & Clyde; NIV, non-invasive ventilation; PROs, patient-reported outcomes; SMS, Short Message Service.

The COPD digital service components being used in the RECEIVER trial are:

Patient-facing web portal: this has been co-designed with patients and captures PROs and provides access to standard COPD self-management content. It also includes a messaging facility which can be patient or clinician initiated. Examples of visuals available on supporting website (https://support.nhscopd.scot).Patient wearable device: Fitbit Charge 3 device (CE marked).Remotely monitored home NIV: provision of this is our current standard of care for patients with hypercapnic respiratory failure, using AirView NIV remote management platform (ResMed). We have integrated our COPD digital service platform with the AirView platform, so that it acquires the NIV data unmodified for review where available. NIV therapy management will continue to be conducted through the AirView platform: the RECEIVER trial COPD platform is not used to modify or enhance patient NIV therapy.User-designed clinical dashboard: presents integrated data with an aim of facilitating improvement in provision of guideline-based COPD care, and supporting COPD self-management.Patient–clinician asynchronous messaging: to support routine clinical care.NHS GG&C Azure cloud-based digital architecture: this provides and integrates the above services with existing NHS GG&C electronic healthcare systems. Diagram of digital architecture included in online supplemental material 3.

10.1136/bmjresp-2021-000905.supp3Supplementary data

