## Study methods and analysis

### Study design

This study is a prospective observational cohort hybrid implementation and effectiveness study.^26^ It will be performed according to the UK Policy Framework for Health and Social Care Research (2020).^27^ The clinical intervention component is regarded as a phase IV adoption study. Data visualisation to facilitate guideline-based care, supported self-management and home NIV are evidence-based COPD interventions.

In this study, we will evaluate the adoption of digitally integrated remote management service innovations to support routine clinical care. Implementation of these will be evaluated and the digital innovations will be iterated to optimise them, based on user experience accrued during the study. We will acquire a consented dataset for trial endpoint analysis including exploratory machine learning-based predictive modelling. The machine learning analysis will also allow us to prioritise data inputs for follow-up study.

Secondary outcomes for the RECEIVER cohort will be compared with those from matched cohorts of patients acquired from the NHS GG&C SafeHaven dataset. Ethics approval is in place to access this large database of de-identified data, to establish a control cohort from a historical time series and a RECEIVER trial concurrent time series. These cohorts will be matched for demographics, COPD severity and hospital admission frequency with the RECEIVER cohort.

We will conduct a substudy of additional baseline and follow-up physiological measurements (oscillometry, parasternal electromyography (EMG), home pollution monitoring) in patients in whom it is feasible to obtain these during their hospital admission and/or hospital attendance alongside their routine clinical care.

Additionally, we will conduct a substudy of clinical users, with platform tracking analytics to measure clinician time spent on the platform, and user experience data. Clinical team members involved in the delivery of patient support using the digital service will be eligible for inclusion and appropriate consent will be sought. The qualitative components will be acquired through semistructured group or 1:1 interviews conducted by trained members of the research team. Thematic analysis will be performed. Anonymised transcripts will be coded, and themes generated from the codes. Themes will be discussed within the research team to reach agreement and add rigour.

An overview of the study design is provided in figure 2.

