### Patient portal support materials, care plans and clinical decision support

The patient web portal will contain linked content to NHS GG&C smoking cessation, vaccination, inhaler therapy, pulmonary rehabilitation, breathing control and ‘my lungs, my life’ COPD support literature, all to aid self-management.

The patient resource within the patient portal will contain a structured exacerbation self-management care plan. This is a digitalised version of the paper structured self-management plan without any change in format or content. Participants will be empowered to activate their own self-management plan or supported/directed to activate this with patient–clinician communication, as standard routine clinical care: the data access, visualisation and patient–clinician messaging facilities in this study will however enhance this.

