## Statistics and data analysis

Secondary outcomes in the RECEIVER observational cohort will be compared with matched retrospective data from de-identified linked datasets of historical control and contemporary control high-risk patients with COPD. These will comprise of patients identified from coding and admission data as having had severe exacerbation of COPD between 1 January 2010 and 30 April 2019 (historical cohort) and between 1 July 2019 and 30 June 2020, excluding participants enrolled in the RECEIVER Study (contemporary control). The historical control dataset will contribute to machine learning models development. Secondary outcome analysis will be separately compared between the RECEIVER cohort, historical cohort and contemporary control cohort. This component of the study is also separately registered with dataset access approval from NHS GG&C SafeHaven LPAC.

The clinical endpoint data will be reported as a proportion and 95% CI for that outcome, calculated by Kaplan-Meier method. Demographic data will be presented as mean and SDs, or medians and IQRs as appropriate. Correlation, t-test, analysis of variance and effect size analyses will be used as appropriate for secondary endpoint analysis, comparing results of clinical endpoint and patient-centred outcomes with NIV therapy and supported self-management parameters.

Machine learning ensemble methods will be used to develop binary classification problems for patient risk. Precision, recall, accuracy and C-statistics of the receiver operating characteristic curve will be used to evaluate model performance.

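### Home NIV uptake is compared with controls who had no home NIV entry route, and supported self-management relies on measures that exist only for platform users

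*Protocol article*

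**What the plan says.** All places are in the protocol article.

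- **Outcome.** Table 1 (Study outcome measures) sets out clinical outcomes to be compared with the two SafeHaven cohorts. One is "Treatment uptake (where indicated): smoking cessation; pulmonary rehabilitation; vaccination; supported self-management; home oxygen; home NIV".
- **Entry to RECEIVER.** Study population gives two routes. One is "Home NIV cohort: hypercapnic respiratory failure and/or sleep disordered breathing, meeting established criteria for provision of home NIV". The other is "Exacerbation cohort: presentation within last 12 months with severe or life-threatening exacerbation of COPD". The abstract describes the first route as covering "chronic hypercapnic respiratory failure requiring home non-invasive ventilation (NIV) or continuous positive airway pressure (CPAP".
- **Selection of controls.** Statistics and data analysis defines both control cohorts as "patients identified from coding and admission data as having had severe exacerbation of COPD", over two date ranges. No hypercapnia or NIV route is given.
- **Matching.** Study design states: "These cohorts will be matched for demographics, COPD severity and hospital admission frequency with the RECEIVER cohort".
- **How NIV is started.** Remote-monitored home NIV says that people with standard indications begin it as routine care. The list of digital service components adds that "the RECEIVER trial COPD platform is not used to modify or enhance patient NIV therapy".
- **Self-management.** The section on portal support materials says: "The patient resource within the patient portal will contain a structured exacerbation self-management care plan". It also says that this is the existing paper plan in digital form. The measures in Table 1 include page views, message threads and rescue packs captured through the weekly questionnaires. Secondary endpoint measures says that supported self-management is captured within the digital platform.

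**The concern.** For home NIV, the route by which some people enter RECEIVER is closely tied to the outcome, and controls have no equivalent route. People recruited because they meet criteria for home NIV are likely to be on it, or about to start it, under routine care. A group chosen only for a severe exacerbation will contain fewer such people. Matching on demographics, severity and admission frequency need not correct this.

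Supported self-management has a different fault. Several of its listed measures are by-products of using the platform, so there is no counterpart to count in the controls.

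At stake is a report that the digital service raised uptake of these two treatments, when part or all of the difference comes from who was recruited or from what could be recorded. Uptake matters to the study's reasoning: Sample size projects fewer admissions on condition that evidence-based care is successfully supported.

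**Working it through.** The article gives no uptake rate, no share entering by the NIV route, and no alpha or power for uptake. The 400 participants are a feasibility figure. There is therefore no stated result to reproduce, and every rate below is an assumption. All cases suppose that the service has no effect.

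**Step 1. Set the definitions side by side.** RECEIVER has a home NIV route or an exacerbation route. Controls have an exacerbation only. The named matching variables do not include NIV status, NIV indication, hypercapnia or sleep-disordered breathing. The outcome has no restriction to people not already on NIV. The indication qualifier is the only protection.

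**Step 2. What if the qualifier were ignored (all patients in the denominator)?** Let *f* be the share entering by the NIV route, *u* the uptake in that route, and *q* the uptake among everyone else in both groups.

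Difference = [*f·u* + (1 − *f*)*q*] − *q* = *f*(*u* − *q*)

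With *u* from 80 to 100% and *q* from 10 to 2%:

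| *f* | Smallest | Largest |
|---|---|---|
| 5% | 0.05 × 0.70 = 3.5 points | 0.05 × 0.98 = 4.9 points |
| 10% | 0.10 × 0.70 = 7.0 points | 0.10 × 0.98 = 9.8 points |
| 30% | 0.30 × 0.70 = 21.0 points | 0.30 × 0.98 = 29.4 points |

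With 400 per group (the control number is assumed) and a two-sided 5% test, the chance of a significant difference is 34 to 92% at *f* = 5% and 83 to 100% at *f* = 10%.

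**Step 3. Apply the qualifier, but let indication be less certain in controls.** Let *v* be the proportion of controls counted as indicated who truly are, with no NIV in the rest, and let true uptake *u* be equal in both groups.

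Difference = *u* − *u·v* = *u*(1 − *v*)

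- *v* = 1: 0 points.
- *v* = 0.9, *u* 80 to 95%: 0.80 × 0.10 = 8.0 to 0.95 × 0.10 = 9.5 points.
- *v* = 0.7, *u* 80 to 95%: 0.80 × 0.30 = 24.0 to 0.95 × 0.30 = 28.5 points.

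**Step 4. Apply the qualifier, but count existing users.** Let *g* be the share of indicated RECEIVER participants already on NIV at entry. The rest have the control uptake *u*.

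Difference = [*g* + (1 − *g*)*u*] − *u* = *g*(1 − *u*)

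- *g* = 0: 0 points.
- *g* = 0.25, *u* 70 to 30%: 0.25 × 0.30 = 7.5 to 0.25 × 0.70 = 17.5 points.
- *g* = 0.5, *u* 70 to 30%: 0.5 × 0.30 = 15 to 0.5 × 0.70 = 35 points.

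The built-in difference is therefore zero when indication is ascertained identically and existing users are left out. The article states neither condition.

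**Step 5. Can indication be recovered in the controls?** The SafeHaven items under EHR data include laboratory results, coded diagnoses and lung function, so some indications may be. No sleep study or NIV record is listed, although overlap with sleep apnoea and nocturnal hypoventilation are among the routine indications. Equal ascertainment is doubtful but not excluded.

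**Step 6. Self-management.** Page views, message threads and weekly portal questionnaires do not exist for people outside the platform. The EHR data list names no self-management record. Other measures on the same line, such as sputum microbiology, are not confined to the platform.

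**The case against.** The strongest reply is that the protocol admits people by indication and not by receipt of NIV, and counts uptake only where indicated. Among people with an indication, uptake is a fair outcome. Most participants are expected to be recruited during an acute admission, so they should resemble the controls, some of whom will also have hypercapnic failure. Definitions of indication and of new versus existing use are commonly left to an analysis plan. Study limitations also disclaims definitive proof.

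Much of this stands, and it rules out three stronger readings.

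- **That home NIV uptake is higher in RECEIVER by construction, by a figure one can state.** With 100% uptake in the NIV route and 5% elsewhere, one gets 0.20 × 0.95 = 19 points if 20% enter that way, and 0.40 × 0.95 = 38 points at 40%. Those figures need an all-patient denominator, which Table 1 does not use, and shares the article does not give.
- **That enrolment is itself uptake of supported self-management.** The portal gives access to a plan that participants may or may not activate, and the primary endpoint asks whether enrolees use the service at all. The same plan exists on paper in usual care, so control uptake is not zero.
- **That the platform cannot affect NIV uptake because it does not alter NIV therapy.** That sentence concerns the management of therapy, not whether people start it.

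What the reply does not remove is the combination fixed in this document: an NIV route on one side only, matching that does not name it, and an outcome open to existing users. The general statement on bias does not mention this overlap.

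**Conclusion.** The concern holds in a limited form. The home NIV comparison favours RECEIVER through cohort selection, unless indication is established identically in both groups and existing users are excluded. The size cannot be derived from the article. The indicated-denominator cases worked above run from 0 to 35 points on assumed inputs and show only that modest departures from those conditions matter. The direction rests on RECEIVER having the larger share of existing users or the more certain indications. It could reverse if, for example, indication in controls were inferred from receipt of NIV, which the article does not propose.

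For supported self-management the fault is non-comparable measurement, not a guaranteed excess. Smoking cessation, pulmonary rehabilitation, vaccination and home oxygen are not touched by this point.

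**What to change.** In Table 1:

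- Compare home NIV uptake only as new starts in the 12 months after index. Restrict it, in both groups, to people who meet the same severe-exacerbation criterion and were not on home NIV or CPAP at index, with indication defined identically from SafeHaven data.
- If prior NIV or indication cannot be identified in SafeHaven, report home NIV uptake descriptively for RECEIVER only.
- Report platform-measured supported self-management within RECEIVER only.

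The restriction should rest on the shared criterion and not on entry route. Controls have no entry routes, so dropping NIV-route participants from RECEIVER alone would remove indicated non-users from one side and leave their counterparts on the other.

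The cost is endpoint wording, a smaller denominator for home NIV and one fewer controlled comparison. Recruitment and clinical care do not change.
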